### Statistical analysis

Statistical analyses for this study will reflect the sampling design, the data collection process, and the research objectives as stated previously. Due to the typically highly skewed distributions of time to diagnosis or treatment, standard methods for transforming the time intervals such as the geometric mean or comparing median times, will be used in the analyses. Crude and adjusted logistic and multinomial regression analyses of dichotomous and ordinal outcomes respectively, will be used to assess the contribution that independent factors have on men's choice of treatment. We will also investigate the representativeness of the study cohort compared to the rest of the men diagnosed with prostate cancer by comparing the distributions of those clinical and demographic variables collected from the Queensland Cancer Registry.

Previous studies looking at patterns of diagnosis and treatment have focussed on the individual-level data, or ecological studies. In order to appropriately investigate whether the observed patterns are due to the characteristics of the cancer patients themselves, or the characteristics of the geographical areas in which the individuals live, it is important to be able to quantify the variation between areas in terms of their diagnostic and treatment profiles. Thus using a multilevel analytical design we can then determine whether the observed variation is due to the clustering of individuals (i.e. a composition effect) or the environmental characteristics of the areas (i.e. a context effect).

We have previously described the advantages of incorporating a multilevel perspective [32]. We will use multilevel models to assess whether geographic remoteness and area-level disadvantage were associated with prostate cancer outcomes after controlling for individual-level socio-demographic characteristics. These models will be fitted using MLwiN version 2.15 (University of Bristol, United Kingdom).

There will be three stages in the model building process. The first is the null model that including individuals (level 1) nested in SLAs (level 2), there are no individual- or area-level variables in the fixed part of this model. If there is a significant SLA-level random term (indicated using Wald chi-square) then this is evidence supporting significant between-SLA variation in the prostate cancer outcome. Second, the null model will be extended by including individual-level factors (patient characteristics, disease stage, co-morbidity, and access to health care and treatment services) as fixed effects. This will inform us as to how much of the area-variation in prostate cancer outcomes is due to these individual-level (compositional) factors, and also assess the contribution of each individual-level factor. Thirdly, the area-level measures such as geographic remoteness and area socioeconomic disadvantage will be included in the model as fixed effects, to quantify how much of the area-variation in prostate cancer outcomes is due to these factors (independent of individual-level factors). Subsequent models will also consider the cross-level interactions between the individual-level and area-level factors.

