### Participants

#### Study cohort

All men newly diagnosed with prostate cancer in Queensland between 1st February 2005 and 31st July 2007 were potentially eligible for the study. Urologists referred eligible men to the study if they were newly diagnosed with prostate cancer irrespective of stage of disease. The following exclusion criteria were used: previous diagnosis of prostate cancer; inability to read, write and speak English; history of dementia, head injury or psychiatric illness; and no regular access to a telephone.

In all, 1291 men were referred to the study, with 1064 men (82.4% of referrals) eligible and agreeing to participate. Figure 1 shows the flowchart of ineligible/excluded men, completeness of data collection and attrition from the study between recruitment and 12 months post-treatment.

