#### Power calculations

Cohort sample sizes were initially determined in order to calculate differences in binomial proportions between two equally-sized subgroups. Assuming pooled variance, two-sided Z-test at 5% significance level, subgroup sample sizes of n = 500 men achieve 80% power to detect at least an absolute difference between the subgroup proportions of 9%.

Power calculations for the variation between and within area units (using *Optimum Design *software[33]) are based solely on the approximate number of clusters (statistical local areas) and records per cluster. The study cohort covers 270 area units (SLAs), with between 1 and 66 (mean 3.9, median = 2) respondents in each unit. Assuming 270 clusters with an average of 4 records per cluster and a baseline proportion of 50%, this gives 80% power at 0.05% significance to detect a difference in proportions between two subgroups of 11%.

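### The Wald chi-square test of the SLA variance is severely conservative, so a non-significant result is weak evidence that areas do not differ

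*Protocol article*

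**What the plan says.** The Statistical analysis section of the protocol article builds the multilevel model in three stages. The first has "individuals (level 1) nested in SLAs (level 2), there are no individual- or area-level variables in the fixed part of this model". For that stage the criterion is: "If there is a significant SLA-level random term (indicated using Wald chi-square) then this is evidence supporting significant between-SLA variation". The section mentions no halved p-value, mixture reference or likelihood-ratio alternative.

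The software is named ("These models will be fitted using MLwiN version 2.15"), but the estimation method is not.

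The Power calculations section describes the data on which the test would run: "The study cohort covers 270 area units (SLAs), with between 1 and 66 (mean 3.9, median = 2) respondents in each unit". The two power figures there concern a difference in proportions between two subgroups. Neither concerns the variance test, and no ICC is given.

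**The concern.** A variance cannot be negative. Under the null hypothesis of no area variation the true value therefore sits on the edge of the parameter space, and a large share of the estimates are exactly zero. The squared ratio of estimate to standard error then does not follow chi-square on 1 degree of freedom. The error runs in one direction: the test rejects far less often than its nominal 5%, and it loses power in return.

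Variation between areas and its determinants are the subject of the second and third study aims, and inequalities are the subject of the fourth. A test that rarely detects small to moderate area variation is a poor instrument for that purpose, and a better one is available on the same data.

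**Working it through.** **Inputs from the article.** 270 SLAs, 1 to 66 men each, mean 3.9, median 2, baseline proportion 50% (Power calculations); 1064 men (Study cohort); two-level null model and Wald chi-square (Statistical analysis). Check: 1064/270 = 3.94, which agrees with the stated mean.

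**Assumed.** ICC from 0 to 0.20; a second outcome proportion of 20%; SLA sizes beyond the stated summaries; normal random effects; maximum-likelihood fitting.

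**The plan's own figures.** No power is stated for the variance test, so there is nothing to reproduce directly. Of the two subgroup figures:
- Without clustering, 500 per subgroup and 50% against 59% give 81.6% power at two-sided 5%, so the 9% difference reproduces.
- With clustering, take 540 men per subgroup and design effect 1 + 3 × ICC. The detectable difference at the printed 0.05% level is already 13.0% with ICC 0. At 5%, the stated 11% needs an ICC of about 0.23: 540/(1 + 3 × 0.23) = 540/1.69 ≈ 320 effective men per subgroup. The printed level is a separate matter.

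**Formulas.** The model is logit(p_j) = b + u_j, with u_j ~ N(0, v). ICC = v/(v + π²/3), so v = 3.29 × ICC/(1 − ICC): 0.173 at ICC 0.05 and 0.366 at ICC 0.10.
- Wald: W = v̂²/Var(v̂), compared with 3.84 (or with 2.71 if the p-value is halved).
- Likelihood ratio (LR): T = 2[l(v̂) − l(0)], with p = ½ P(χ²₁ > T). The 5% critical value is 2.71.

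If the boundary were the only problem, W would exceed 3.84 in about ½ × 5% = 2.5% of null samples, and halving the p-value would repair it. However, the standard error of v̂ grows with v̂, so W rises slowly even when the estimate is large. The level therefore falls further.

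**Main simulation, binary outcome.** 1064 men, 800 replicates per setting, 25-point quadrature. The assumed sizes have 134 SLAs with one man, 45 with two, 90th percentile 9 and maximum 66. All columns use the same data sets; entries are rejection rates.

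| Proportion | ICC | Wald, 3.84 | Wald, 2.71 | LR, 3.84 | LR mixture, 2.71 |
|---|---|---|---|---|---|
| 50% | 0 | 0% | 0.3% | 1.5% | 3.9% |
| 50% | 0.02 | 2% | 7% | 19% | 29% |
| 50% | 0.05 | 28% | 51% | 68% | 77% |
| 50% | 0.10 | 81% | 90% | 96% | 98% |
| 50% | 0.15 | 96% | 98.5% | 99.5% | 99.6% |
| 20% | 0 | 0% | 0.4% | 1.3% | 4.0% |
| 20% | 0.02 | 1% | 5% | 15% | 22% |
| 20% | 0.05 | 12% | 25% | 47% | 55% |
| 20% | 0.10 | 50% | 71% | 84% | 91% |
| 20% | 0.15 | 83% | 93% | 98% | 99% |

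At ICC 0.20 the Wald test reaches 99.9% (50%) and 96% (20%). With zero variance, 62% of fits gave an estimate of zero. Zero rejections in 800 puts the level below about 3/800 = 0.4%.

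At ICC 0.05 and proportion 50%, the gap between the stated test and the mixture LR test is 77 − 28 = 49 points. Of these, 68 − 28 = 40 come from the form of the statistic and 77 − 68 = 9 from the reference distribution.

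**Continuous outcome.** Linear mixed model, 1054 men, 3000 replicates. The Wald test at 3.84 rejects in 0.27% at ICC 0 (1.4% with the p-value halved), 9% at 0.02, 55% at 0.05 and 97% at 0.10. The mixture LR test gives 3.6%, 36%, 84% and 99.6%.

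**Further runs on sizes matching the same summaries.**
- 1000 replicates, proportion 50%, v = 0.15, 0.25 and 0.40 (ICC = v/(v + 3.29) = 0.04, 0.07 and 0.11): Wald level 0.0%, power 19%, 49% and 85%; mixture LR level 3.4%, power 58%, 82% and 98%.
- A smaller run: 0 of 300 Wald rejections at zero variance. At ICC 0.05 the Wald test had 24% power (proportion 50%) and 9% (20%), against 67% and 40% for the mixture LR test.
- Across all runs at ICC 0.10, the lowest values were about 40% for Wald and 76% for mixture LR.

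**What ICC 0.05 means.** SD = √0.173 = 0.416. With a 50% outcome, the middle 95% of SLAs span logits of ±1.96 × 0.416 = ±0.815, that is, true proportions from 31% to 69%.

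**The case against.** Much can be said for the plan, and most of it stands.

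- **The error is conservative.** The article draws only the positive inference, that a significant term supports area variation, and that inference remains sound.
- **A reader might infer that the test gates the later stages.** It does not. Stages 2 and 3 are described without any condition on stage 1, and the effects of remoteness and disadvantage in stage 3 are fixed effects that this test does not judge.
- **A reader might infer that a null result will be presented as equity.** No section says so.
- **A reader might conclude that power is very low in general, because half the SLAs have two men or fewer.** Neither part holds. Power is very low only for small variation, and at ICC 0.15 it is at least 83% in the main simulation. The LR test does much better on the same sparse data, so the median of 2 is not the cause; the larger SLAs carry most of the information. At ICC 0.02 no test does well: the mixture LR test has 22-29% for a binary outcome.
- **The 11% figure, read at 5%, could suggest that a large ICC was expected.** Near ICC 0.20 the Wald test is adequate. But the article states no ICC, the back-calculation rests on a simple design effect, and 11% is not reached at the level actually printed. It cannot carry that inference.
- **The estimator is not stated.** Quasi-likelihood or MCMC could change the figures.

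Silence about halving does not help the plan, since the halved version is also far below its level. The objections narrow the consequence but do not supply a valid test.

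**Conclusion.** The concern holds as a point about the stated test. With the article's SLA structure and maximum-likelihood fitting, the Wald chi-square has a type I error of about 0% for binary outcomes and about 0.3% for a continuous one, against a nominal 5%. A significant result is credible. A non-significant one is weak evidence of no area variation.

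For a binary outcome at ICC 0.05, power is about 9-28%, against about 40-77% for the mixture LR test. At ICC 0.10 it is about 40-81% against 76-98%. By ICC 0.15 to 0.20 the gap is small or gone. For a continuous outcome the loss is milder: 55% against 84% at ICC 0.05.

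The direction follows from the boundary and the form of the statistic. The sizes rest on the assumed ICC, the assumed SLA size distribution beyond the stated summaries, normal random effects and the assumed estimator.

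**What to change.** Replace the Wald criterion with a likelihood-ratio test of the SLA variance against the 50:50 mixture of chi-square(0) and chi-square(1) (critical value 2.71 at 5%), from a full-likelihood fit. Alternatively, fit by MCMC and report the posterior of the variance. State the estimation method either way.

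In both cases report the ICC or median odds ratio with its interval, and state that a non-significant term will not be interpreted as absence of area variation.

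The cost is a sentence or two of text, a little more computing and possibly a different estimation routine, since a likelihood-ratio test needs a true likelihood. No new data are needed.

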#### Remoteness

Remoteness of residence when diagnosed with breast cancer was categorized using the ARIA+ classification [22], which categorizes remoteness into Major City, Inner Regional, Outer Regional, Remote and Very Remote areas. The ARIA+ classification is a purely geographic measure that considers road distance measurements from localities, and is a measure of accessibility and remoteness.

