##### Road travel distance calculations

Distances between patients, diagnostic centres, treatment facilities and other medical centres will be calculated directly from the geo-coded latitude and longitude points. Many studies assessing distance to treatment have calculated straight line distances [25-31], however this method may under-estimate travel times [29], illustrating the importance of using accurate road distance and travel time information [25,27]. These road distances and times will be calculated using commercial GIS software, combined with street network analysis and display tools: and custom GIS applications to enable calculation of the closest road travel distance between one location (such as patient's residence) and multiple locations (such as various treatment facilities).

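### The staged model estimates remoteness net of access to care and calls the area variation that access explains compositional, so any part of the remoteness effect acting through geographic access is left out

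*Protocol article*

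**What the plan says.** The Statistical analysis section of the protocol article sets out three stages: a null model with men nested in Statistical Local Areas (SLAs), a model with person-level terms, and a model with area measures added.

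- **Stage 2** adds "individual-level factors (patient characteristics, disease stage, co-morbidity, and access to health care and treatment services) as fixed effects". It is meant to show "how much of the area-variation in prostate cancer outcomes is due to these individual-level (compositional) factors".
- **Stage 3**: "the area-level measures such as geographic remoteness and area socioeconomic disadvantage will be included in the model as fixed effects". The result is read as area variation "due to these factors (independent of individual-level factors". The only further models named are cross-level interactions.
- **Earlier in the same section**, the multilevel models are described as testing whether remoteness and area disadvantage are "associated with prostate cancer outcomes after controlling for individual-level socio-demographic characteristics". Access, disease stage and co-morbidity are not named there. The same passage separates composition, the clustering of individuals, from context: "or the environmental characteristics of the areas (i.e. a context effect").
- **Remoteness** describes ARIA+ as a "purely geographic measure that considers road distance measurements from localities, and is a measure of accessibility and remoteness".
- **Road travel distance calculations** plans the "closest road travel distance between one location", such as the patient's home, and several others, such as treatment facilities.

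**The concern.** Distance to services is a feature of where a man lives, so on the article's own definition it belongs to context. If the stage 2 access term is distance of this kind, two things follow.

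First, the remoteness coefficient at stage 3 compares men in more and less remote areas who have the same access. Any disadvantage that arises because services are far away is removed from it.

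Second, the fall in between-SLA variance at stage 2 is reported as due to the kind of men living in each area, when part of it is due to the area.

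Aim 2 is to explain area-level variation in diagnostic and treatment pathways, and Aim 4 is to identify inequalities in them for policy. A weak stage 3 remoteness term could be read as little geographic inequality when it shows only that little remains once access is held equal.

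**Working it through.** No figure in the article bears on this point, so there is none to reproduce. The check is a comparison of the texts, followed by an illustration on assumed values.

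**1. The texts side by side.** The general description of the multilevel models adjusts for socio-demographic characteristics. The staged description adjusts for patient characteristics, disease stage, co-morbidity and access. These are different adjustment sets for what reads as the same models. No stage contains remoteness without access.

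**2. Is access individual or contextual?** ARIA+ is built on road distance and described as an accessibility measure. The planned travel distances run from each patient's residence. Under Geocoding of street address information, the SLA centroid replaces a patient's address when the full address is missing. For those men, distance to a given facility is constant within the SLA, so it is an area variable.

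**3. What the coefficient becomes.** On a linear scale, total remoteness effect = direct effect + effect through access. With access in the model, the remoteness coefficient is (1 − share through access) × total. Carried to the log odds scale with an assumed total odds ratio of 2.0, the retained odds ratio is exp(ln 2 × (1 − share)):

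| Share through access (assumed) | Retained odds ratio |
|---|---|
| 0% | 2.00 |
| 50% | 1.41 |
| 70% | 1.23 |
| 90% | 1.07 |

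This is approximate, because odds ratios are non-collapsible.

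**4. Precision.** Treating remoteness as one continuous covariate with correlation r to access, its standard error is multiplied by 1/√(1 − r²). For assumed r of 0.6, 0.8 and 0.9 this gives 1.25, 1.67 and 2.29. With five ARIA+ categories it is only a rough guide.

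**5. Variance attribution.** A small simulation used 270 SLAs (the article's number), about 965 men on average, and 12 replicates. The outcome was continuous. Remoteness R was an area variable with variance 1, and person-level access was A = 0.8R + 0.6 × noise. The outcome was y = cR + bA + SLA effect (SD 0.2) + residual (SD 1), with c = 0.30 × (1 − share) and b = 0.30 × share / 0.8. The total effect is therefore 0.30 throughout, and the expected coefficients with access in the model are 0.30, 0.15 and 0. All values except the 270 are assumed.

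| Share through access | R coefficient, without access | R coefficient, with access | SLA variance: null | Access only (stage 2) | Access + R (stage 3) | R only |
|---|---|---|---|---|---|---|
| 0% | 0.31 | 0.32 | 0.121 | 0.053 | 0.030 | 0.030 |
| 50% | 0.31 | 0.17 | 0.119 | 0.033 | 0.030 | 0.027 |
| 100% | 0.31 | 0.02 | 0.117 | 0.029 | 0.030 | 0.030 |

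Stage 2 absorbs (0.121 − 0.053)/0.121 = 56%, (0.119 − 0.033)/0.119 = 72% and (0.117 − 0.029)/0.117 = 75% of the null SLA variance. Stage 3 then removes a further 0.023, 0.003 and about 0. Even in the first row, where access has no effect of its own, it stands in for remoteness, and more than half of the area variance would be labelled compositional. Remoteness alone brings the variance to about 0.03 in every row.

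**The case against.** The strongest objection is that access is never defined. The article also collects non-geographic variables that could serve: health insurance, public or private status of the treating facility, and use of general practitioner and specialist services. Road distance is described within the area-level part of the article, so on a literal reading it might enter at stage 3. This stands as a limit: the concern applies only to the extent that the term is geographic. It does not remove the point. The wording covers access to treatment services, and the article plans person-level distances to treatment facilities. If distance did enter at stage 3 beside remoteness, the compositional label would not arise, but the remoteness coefficient would still be net of distance.

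It is also fair to say that ARIA+ and distance to a cancer facility are not the same thing. One of the two tertiary centres is in Townsville, and the documents give no correlation. A reader might infer that access simply is the remoteness exposure; the documents do not establish that.

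A conditional effect is a legitimate quantity, and the article declares it openly. That stands, but it is not the total area inequality that Aims 2 and 4 call for. The crude and adjusted regressions of treatment choice, and the sentence naming only socio-demographic adjustment, may yield remoteness without access. However, the former are not said to include remoteness, and the latter conflicts with the staged description.

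Three stronger readings are tempting and not supported:

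- **That entering access before remoteness biases the coefficient.** Order does not change the final stage 3 coefficient; the presence of access does. Order affects only how variance is attributed.
- **That the plan reverses the answer to Aims 2 to 4.** The attenuation may be nil, Aim 2 also covers individual-level determinants, and a strong distance effect beside a weak remoteness effect would itself reveal inequality.
- **That disease stage should also leave the main model.** It may be partly downstream of access, but for treatment outcomes it is case mix, and dropping it could make differences in clinical need look like inequity.

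**Conclusion.** The point holds in a conditional form. As written, no stage gives remoteness without access, the two descriptions of the adjustment set disagree, and variance explained by access is called compositional although geographic access is contextual on the article's own definition. If access is geographic, the stage 3 remoteness effect omits the part that acts through it. The size runs from none to nearly all and cannot be narrowed from the documents. The odds ratio of 2.0, the shares, the correlations and the simulation settings are assumptions that show the range, not estimates for this cohort. The variance misattribution is less dependent on the share: at the assumed correlation of 0.8, stage 2 took 56% to 75% of the SLA variance across the whole range.

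**What to change.** 1. Reconcile the two descriptions of the adjustment set in the Statistical analysis section, and state which variables make up access.
2. Fit remoteness and area disadvantage adjusted for patient characteristics and case mix (co-morbidity, and disease stage where treatment is the outcome), without geographic access. Use this model for conclusions about area inequality.
3. Add access or travel distance in a separate further step, reported as mechanism. Present the remoteness coefficient from this step as the part not acting through access.
4. Do not call the area variance explained by geographic access compositional. Non-geographic person-level items such as insurance can stay with patient characteristics.

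The cost is one extra model per outcome and some rewording. All the variables are already collected or planned.
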